## Abstract

Infectious animal diseases represent a major constraint to livestock productivity, food security and wellbeing in many developing countries. To mitigate these impacts, farmers frequently use antimicrobials without professional advice, potentially yielding drug residues in livestock products and the food chain, as well as resistant antimicrobial genes. Recent studies identified Contagious Bovine Pleuropneumonia (CBPP) and Peste des Petits Ruminants (PPR) as the diseases most negatively affecting ruminant livestock productivity and farmers’ wellbeing in Ghana. Despite the approval and availability of effective CBPP and PPR vaccines in Ghana, acceptability, affordability, accessibility, and availability of vaccination limit their uptake, with only 15% of farmers regularly vaccinating their herds. During formative qualitative research to identify barriers and potential intervention options, farmers suggested that establishing localized farmer intervention platforms could improve vaccine access. The main idea is the platforms enabling information exchange on livestock vaccines, enhancing service scheduling, and sharing vaccination costs among farmers living in the same locality. We now wish to test formally this hypothesis.

Through a cluster-randomized controlled trial, we aim to determine the effect of localized farmer platforms on animal vaccination uptake (primary outcome), antimicrobials use in livestock production, disease-induced mortality in livestock, and livestock farmers’ wellbeing (secondary outcomes). The intervention will be randomized at the community level. The study will involve 460 farming households across 46 rural communities (study clusters). Clusters will be randomized with equal probability to treatment and control (23 communities each). Approximately 10 households per community will be sampled for data collection at baseline, and at 6 and 12 months post-intervention, following prevailing vaccination schedules. We will conduct an intention-to-treat analysis using the available case population. The findings will inform strategies to tackle the impact of infectious livestock diseases on food security, public health and farmers’ wellbeing.

**Trial registry**: https://pactr.samrc.ac.za/; ID No.: PACTR202405854213937.

## Introduction

1

In low-and-middle income countries (LMICs), animal diseases are highly prevalent and poorly controlled due to low performance of veterinary services and limited farmer engagement, resulting in significant herd mortalities [1]. On average, about 7% of adult cattle, 21% of calves, 15% of adult sheep and goats, and 23% of lambs and kids die from animal diseases annually in the least developed countries [2]. In LMICs, majority of households are smallholders earning less than USD 60 monthly in agricultural income [3]. In contrast, the average market value of ruminant livestock in Africa ranges between USD 120 for one sheep or goat and USD 600 for one cattle [4]. The livestock losses negatively affects productivity of the livestock sector, livelihoods of farming households and contributes to food insecurity, particularly for vulnerable households in LMICs [5]. Disease-related mortalities also adversely affect farmers’ wellbeing, particularly on the psychological, physical, and social domains [[6], [7], [8]].

What is more, veterinary services delivery has been ineffective in many LMICs in practice, due to inadequate public investment in the veterinary sector, with significant shortfalls in human and material resources [9]. This lack of investments is often attributed to the implementation of drastic structural adjustment policies during the 1980s aimed at addressing high indebtedness levels of LMICs [10]. In addition, veterinary medicines are poorly regulated. A recent review showed that 80% of African countries lack capacity to control the registration, import and production, distribution and usage of veterinary medicines. There is also a lack of drug residue testing programmes in more than two-thirds of the countries [11]. Thus, an overwhelming majority of farms use antimicrobials regularly, without professional advice [12,13].

The high usage of antimicrobials coupled with a lack of residue testing programmes and inadequate regulatory capacity within the food chain, could foster the persistence of drug residues in livestock products, especially when treated livestock are slaughtered prior to recommended withdrawal periods, and accelerate the development of related antimicrobial resistant pathogens [14,15]. Given the apparent shortfalls in veterinary resources, a reduction in occurrence of diseases, particularly through disease prevention strategies, would greatly reduce the disease burden, and workload on veterinary personnel.

Effective control of infectious diseases is mainly achieved with rapid diagnostic tools and effective vaccination strategies [16,17]. However, neither strategy is currently used adequately in practice in many LMICs [11,18]. Studies in Ghana have shown that although livestock farmers and veterinary personnel identify CBPP and PPR as priority diseases affecting herds, only 15% of herds are vaccinated regularly against either disease. In addition, treatments applied by most farmers are not useful for the conditions managed. Consequently, diseases are ineffectively treated, disease-related mortality rates are high, and farmers experience deteriorating wellbeing as severity of disease-related mortalities increased [7,19].

In Ghana, both demand and supply side constraints have been identified to limit vaccination utilization. Demand-side barriers include farmers’ limited awareness of the value of vaccines, and unaffordability issues, especially when farmers must cover entire cost of vaccine vials, even if they do not have enough animals to use an entire vial. The supply-related barriers are mainly due to a limited number of trained veterinary personnel in public and private practice, and the lack of adequate veterinary health infrastructure, which limit accessibility to veterinary personnel’s services when needed [20]. The World Organization for Animal Health (WOAH, founded as OIE) data show that the average veterinary workforce per animal in Africa was approximately 3530 veterinary livestock units (VLUs) in 2019 [21]. Based on the most recent Performance of Veterinary Services (PVS) Gap Analysis conducted in 2011 in Ghana, the ratio of veterinary workforce to animals is substantially lower, more than tenfold less than the African average [22]. There is therefore a need for innovative and sustainable strategies to improve vaccination uptake, for better disease control. During group discussions in formative qualitative research aimed at co-developing sustainable interventions, farmers proposed among other measures that the formation of localized community platforms could address most of the reported challenges with vaccination access [20]. We therefore developed this intervention study to evaluate formally, the effectiveness of this proposed intervention.

## Research objectives, hypothesis and study outcomes

2

The main objective of the study is to evaluate the effect of an innovative community-led intervention on the uptake of CBPP and PPR vaccines by livestock farmers in Ghana, and evaluate the impact of vaccination uptake on antimicrobial use in livestock farming, disease-induced livestock mortalities and farmers’ wellbeing. The study will be a cluster randomized controlled trial, which will introduce the intervention communities to a new Community Action for Vaccination Initiative (CAVI) that is expected to enable farmers to coordinate their livestock vaccination efforts by leveraging the strengths of the local group.

The study hypothesis is that CAVI has an impact on uptake of animal vaccines in farming communities. We also hypothesize that CAVI will have an impact on the usage frequency and quantity of antimicrobials in livestock production, occurrence of disease-induced animal mortalities, and wellbeing of livestock farmers.

The primary study outcome is the uptake for CBPP and PPR vaccines. The secondary outcomes include frequency and quantity of antimicrobials used by farmers, incidence of livestock herd mortalities due to disease, farmers’ wellbeing on the physical, psychological, social, and environment domains, and the acceptability and feasibility to scale of CAVI to the key stakeholders including farmers and veterinary service providers.

## Methods

3

### Study setting

3.1

This study will be conducted in the Mion, Pru East and Kwahu Afram Plains South (KAPS) Districts, which are representative of the northern, middle and southern farming belts of Ghana. The districts lie in the Guinea Savannah, Transition and Deciduous forest Vegetation zones, which are the primary livestock production zones in Ghana [[23], [24], [25]]. The districts were selected purposively in collaboration with the regional directors of veterinary services, using a sampling frame of farming districts located within these vegetation zones. The selected districts are mainly rural and agrarian, with about one-third of the livestock holdings of households being ruminant species. Cattle, sheep, and goats are the predominant ruminant livestock species reared in these districts. Majority of livestock rearing (53%) is for income generation – the rest is directly consumed by households, or used for other socio-cultural purposes. The livestock production system is largely extensive and dominated by small-scale farmers [26].

In rural Ghana, livestock farmers typically obtain approval from community leaders such as chiefs, local assembly members, landowners, or opinion leaders, to keep and graze their animals within the community [27]. Veterinary services in these areas are predominantly provided by veterinary paraprofessionals, who hold a minimum of a diploma in animal health. These paraprofessionals operate under the supervision of district or regional veterinarians, who hold a Doctor of Veterinary Medicine (DVM) degree, and assign them specific operational areas to deliver veterinary services [22].

To ensure resource optimization and sustainability of the intervention, this project will leverage the existing veterinary service and local authority framework within the study setting. In collaboration with the veterinary paraprofessionals assigned to the operational areas within which the intervention communities are located, we will identify individuals in each community to receive the intervention (training). The training will be conducted with support from local staff of the Veterinary Services Directorate and the Department of Agriculture in the study districts.

### Study design

3.2

This will be a two parallel arm cluster randomized controlled trial with, wherein intervention communities will receive the CAVI package, while the control communities will receive the standard of care (individual farmers schedule vaccination with veterinary personnel on their own). The CAVI package entails training and support for selected farmers in the intervention communities to establish local platforms that facilitate scheduling vaccination activities with veterinary personnel. A group-level randomization (1:1) stratified by district was implemented in allocating the intervention to the study communities. The allocation procedures were conducted using R Software [28]. Fig. 1 below illustrates the study design.

**Fig. 1 f0005:**
[figure not shown]
Study design

In one of the study districts, we will evaluate the effect of the provision of an add-on intervention to half of the intervention communities. This add-on intervention entails discount vouchers worth 25%, 50% and 75% of the cost of vaccinating eligible animals in a farmers’ herd. The farmers in the selected communities will ballot for the vouchers during the first local platform meeting. In the selected district, the trained individuals will additionally receive a discount voucher worth 50% of the cost of vaccinating their herd. The discount vouchers provided would be reimbursed to farmers after their payment for the vaccination services provided by the veterinary personnel within the study district. Fig. 2 below the randomization procedures in allocating the intervention.

**Fig. 2 f0010:**
[figure not shown]
Randomization procedures in allocating the intervention

### Intervention (CAVI) description

3.3

The intervention package entails the training of at least two persons per community to build capacity and knowledge in understanding vaccine effectiveness, profitability, safety, and the personal and community-level benefits of vaccination. The training also covers scheduling vaccinations for priority diseases (i.e. CBPP and PPR infections) with veterinary personnel, and herd vulnerability to the diseases. The training comprises two modules designed to equip livestock farmers with the knowledge and skills necessary to establish and manage farmer cooperative platforms, to empower participants to coordinate vaccination of herds within their communities (details available in **Additional file 1**). In summary, Module 1 focuses on the benefits of collective action, emphasizing relationship-building, understanding community dynamics, and the principles of forming and managing cooperatives. Through practical exercises, group discussions, and real-life scenarios, participants will explore the importance of trust, communication, and coordination in achieving shared goals. These activities demonstrate how collective efforts can address individual challenges, improve productivity, and reduce costs associated with vaccination. Module 2 addresses the burden of the priority livestock diseases i.e., CBPP and PPR, and highlights the critical role of vaccination. Participants learn about vaccine schedules and the socio-economic benefits of improving herd health. By fostering collaboration, the intervention empowers farmers to leverage cooperative platforms for enhanced vaccine access, disease prevention, and knowledge exchange, ultimately contributing to improved livestock productivity and community resilience.

The training participants will be purposively selected in collaboration with the local community leaders and veterinary service personnel. The intervention package will be delivered after the baseline survey and reinforced at the midpoint follow-up period (6 months). Each trained individual will receive a register to keep records of local platform members, meeting days and meeting minutes. The trained individuals will each receive mobile airtime worth GHC 50 [USD 5] quarterly to facilitate their efforts in convening meetings and conducting outreach to veterinary personnel.

Since blinding is not possible, to reduce potential imbalance in dropouts between study arms and non-blinding bias, each participating farmer in the surveys in both study arms would also receive a total of GHC 50 mobile airtime over the three rounds of the survey (baseline, mid-point and end-point follow-ups) as an attention control intervention. The trained individuals will be supported to establish their respective local platform of farmers within the intervention communities, and schedule vaccination visits with veterinary personnel. The veterinary personnel will be provided with registers to record all vaccination requests received from farmers, the number of requests honored (in both study arms), and any adverse events following vaccination. In collaboration with the regional veterinary services directorates and district veterinary personnel, the study will ensure that an adequate supply of vaccines and consumables are maintained at the district level to meet the anticipated demand for vaccination services. Additionally, each veterinary personnel will receive quarterly airtime vouchers worth GHC 50 to support their efforts in delivering vaccination services.

A radio sensitization program will be held to inform all livestock farmers in both study arms about the vaccines availability. The program will be broadcast live on local radio stations in each study district, and the recordings repeated over two weeks prior to intervention implementation to sensitize the communities. The broadcasts will be done in the local languages by veterinary personnel in the study districts, with support from the research team. Fig. 3 below shows the theory of the intervention effect.

**Fig. 3 f0015:**
[figure not shown]
Illustration of the hypothesized theory of the intervention’s effect

### Theory of intervention effect

3.4

Please see Fig. 3 for details

### Sample size

3.5

The sample size was estimated with the epiDisplay package in R software [28]. With a sample size of 460 farming households across 23 village clusters per treatment group, the study is powered to detect a difference of 25% to 40% vaccination coverage with 80% power, assuming alpha = 0.05, power = 0.8, intra-cluster correlation coefficient = 0.2, and non-response rate = 10%.

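### The stated 80% power for 25% versus 40% coverage is wrong: 460 households in 46 communities give about 52–55% under the plan's own assumptions

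*Protocol article*

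**What the plan says.** Section 3.5 (Sample size) states that with 460 farming households and 23 village clusters per group "the study is powered to detect a difference of 25% to 40% vaccination coverage with 80% power". The assumptions are listed there: "assuming alpha = 0.05, power = 0.8, intra-cluster correlation coefficient = 0.2, and non-response rate = 10" per cent. The calculation is attributed to an R package; the call itself is not shown.

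The Abstract settles that 460 is the total for both arms: "The study will involve 460 farming households across 46 rural communities (study clusters"), split 23 and 23, and "Approximately 10 households per community will be sampled for data collection at baseline". That is 230 households per arm.

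Section 3.5 names no gain from baseline adjustment, stratification or repeated measurement.

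**The concern.** An ICC of 0.2 is large. With ten households per community it cuts the information in the sample by a factor of nearly three, and once clusters are of moderate size the number of communities limits power more than the number of households does. With 23 communities per arm, a 15-point difference at 80% power looked out of reach, so the statement needed checking.

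This is the only power basis the article gives, and it concerns the primary outcome. If true power is near one half, a real rise from 25% to 40% would be missed nearly half the time. The Conclusion makes scale-up conditional on the intervention being effective, so a non-significant result judged against a claimed 80% could wrongly count against the intervention.

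**Working it through.** **Inputs.** From section 3.5: p1 = 0.25, p2 = 0.40, alpha = 0.05, power = 0.80, ICC = 0.2, non-response 10%. From the Abstract: k = 23 communities per arm and m = 10 households per community, hence m = 9 after non-response. Sidedness is not stated. I take two-sided as the base case, since the hypothesis in section 2 has no direction, and test one-sided as well.

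**Attempt to reproduce the stated figure: required sample size**

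Independent households per arm for 80% power, two-sided:
- pooled-variance formula: 151.9, so 152
- with continuity correction: 164.9, so 165
- unpooled: (0.1875 + 0.24) × (1.960 + 0.842)² / 0.15² = 149.1

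Design effect for m = 10: 1 + (10 − 1) × 0.2 = 2.8.

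| Formula | × 2.8, per arm | ÷ 0.9 for non-response, per arm |
|---|---|---|
| Unpooled | 417.6 | 464.0 |
| Pooled | 425.2 | 472.5 |
| Continuity-corrected | 461.8 | 513.1 |

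The plan has 230 per arm. By the pooled formula, about 43 to 44 communities per arm would be needed at 9 to 10 responders each.

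**Power of the design as planned**

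Effective n per arm = k × m / [1 + (m − 1) × ICC].

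- m = 10: 230 / 2.8 = 82.1. SE = √(0.4275 / 82.1) = 0.0721; 0.15 / 0.0721 = 2.08.
- m = 9: 207 / 2.6 = 79.6. SE = √(0.4275 / 79.6) = 0.0733; 0.15 / 0.0733 = 2.05.

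| | Normal, unpooled | Normal, pooled | t, 44 df |
|---|---|---|---|
| m = 10 | 54.7% | 53.7% | 52.9% |
| m = 9 | 53.5% | 52.4% | 51.7% |

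**Variants that might rescue 80% for 25% versus 40%**

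- One-sided alpha 0.05: 64.5–66.8%.
- 460 read as per arm (20 households in each of 23 communities): 59–61%.
- Unlimited households per community: effective n tends to 23 / 0.2 = 115 per arm, and power to 67–69%. At this ICC, no cluster size brings 23 communities per arm to 80% on a two-sided test.
- Averaging the two follow-up rounds, with an assumed within-household residual correlation of 0.3 to 1: about 54–59%. The between-community variance remains.

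**What the design can support**

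- Detectable at 80% power with m = 9: 25% versus 45.7–46.2%, about 21 points.
- ICC at which 25% versus 40% has 80% power: 0.041–0.049 (m = 9) or 0.053–0.060 (m = 10), so about 0.05.
- Starting from the 15% regular-vaccination figure in the Introduction, 15% versus 30% has about 62–63% power.

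**A possible source.** The per-arm requirement comes close to 460 by two routes: 165 × 2.8 = 462 (continuity-corrected, before non-response) and 149.1 × 2.8 × 1.1 = 459 (unpooled, inflated by 10%). With 46 communities per arm, power would be 82–84%. This fits a per-arm number entered as a total, but the two routes differ and the article does not show its calculation.

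**The case against.** Four points deserve a fair hearing.

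- **Sidedness is my assumption.** True, and it should be stated. One-sided testing raises power only to about 65–67%.
- **The sentence could mean a difference of 25 percentage points, reaching 40%.** The 15% figure in the Introduction plus 25 points is exactly 40%. For 15% versus 40% the design has about 95% power. A design with 95% power is certainly powered for that difference, so this reading would make the sentence conservative rather than false. But the words more naturally name two coverage levels, and 80% does not reproduce on this reading either.
- **The planned analysis is not one binary outcome per household.** Section 3.8.1 also compares the proportion of animals vaccinated per herd, at two time points, with mixed models, and section 3.2 stratifies the randomization by district. A per-herd proportion can vary less than a yes/no outcome. If its variance were half the binomial value (an assumption; the article gives no figure), power at m = 9 would be about 81–83%; at 80% of the binomial value, about 61–63%. This stands as a caution: 52–55% describes the calculation section 3.5 sets out, not necessarily the final model. It does not rescue section 3.5, which claims none of these gains. Nor is adjustment for baseline uptake evident, since section 3.6 lists only antimicrobial use among the baseline data.
- **The per-arm explanation is conjecture.** Agreed. The finding does not depend on it.

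**Conclusion.** The concern holds. On the inputs the article itself gives, 460 households in 46 communities have 52–55% power for 25% versus 40% coverage, not 80%. This rests on a two-sided 5% test, a binary outcome per household at one time point, equal cluster sizes and the stated ICC of 0.2. No standard variant of that comparison reaches 80%. The article would be right only with an ICC of about 0.05, a quarter of the one stated, or for a difference of about 21 points. An unseen analysis plan cannot settle this, because the published inputs and the published power contradict each other.

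**What to change.** Correct section 3.5. Suggested wording:

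> With 23 communities per arm and about 9 responding households per community, the trial has about 52% power (two-sided 5%) to detect 25% versus 40% coverage at an ICC of 0.2. The difference detectable with 80% power is 25% versus about 46%. Power of 80% for 25% versus 40% would require an ICC of about 0.05. A non-significant result will be interpreted through its confidence interval.

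The authors should also state the sidedness and show the calculation. If they relied on a different ICC, a per-herd outcome variance or a precision gain from the model, they should name it with its value and give the power that follows.

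The cost is wording only; the stated power becomes less favourable. Allocation has been carried out (section 3.2) and training delivered (Discussion), and this correction asks for no added recruitment and no change to the design or analysis.
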